### Variables under study

A systematic review of RCTs [24] and an extensive search in the literature and international healthcare organizations (e.g., American Heart Association, Society of Thoracic Surgeons) was conducted to retrieve best-practice guidelines for interprofessional teams in postoperative cardiac surgery settings, and confounding variables related to patient and interprofessional teams’ characteristics. A total of 12 best-practice guidelines and 13 confounding variables were identified and are presented in Fig 1. The operationalization of each variable is presented in S3 Appendix.

**Fig 1 pone.0282467.g001:**
[figure not shown]
The influencing variables and the level of adherence to best-practice guidelines by interprofessional teams with and without acute care nurse practitioners in cardiac surgery.

#### Independent variable: Interprofessional teams with and without acute care nurse practitioners

A dichotomous variable will be created to measure the inclusion of at least one ACNP within the interprofessional team. For patients under the care of an interprofessional team with ACNPs, an additional descriptive variable will measure the number of days where the ACNP was involved in the daily follow-up of the patient, on the entire hospitalization at the postoperative cardiac surgery unit.

#### Dependant variable: The level of adherence to best-practice guidelines by interprofessional teams

A total of 12 best-practice guidelines will be included in this project (Fig 1). All best-practice guidelines are divided into three categories: 1) pharmacotherapy (n = 4), 2) laboratory tests (n = 4), and 3) postoperative assessment (n = 4).

Four best-practice guidelines are included in the category of pharmacotherapy. These guidelines are the prescription and relevant monitoring of medications including: 1) anticoagulants, 2) beta blockers, 3) lipid-lowering agents, and 4) anti-platelets, during hospitalization and at hospital discharge of the patient. The adherence to these four guidelines is defined by the prescription (e.g., beta blocker) and relevant monitoring (e.g., assessment of the blood pressure) of those four medications on a daily basis during the patient’s hospitalization and at discharge. For each best-practice guideline, two additional descriptive variables will be collected, including the type of medication prescribed and the presence of a contraindication, which precludes the possibility of achieving the guideline recommendation (e.g., allergy).

Four best-practice guidelines on laboratory tests are included, recommending the prescription and monitoring of the following: 1) potassium (K+), 2) magnesium (Mg+), 3) serum glucose, and 4) international normalized ratio (INR) by interprofessional teams during the patient’s hospitalization in the postoperative cardiac surgery unit. The achievement of each best-practice guideline recommendation will be confirmed if the laboratory result falls under the normal range supported by the current literature. The monitoring of laboratory tests also includes the interventions conducted by clinicians to ensure the laboratory test values remain within the normal range, such as routinely ordering laboratory tests, assessing laboratory tests to confirm normal values and detect any abnormal values, and performing pharmacological and clinical interventions to address abnormal laboratory test values. An additional variable called “no INR needed” will be added specifically for the best-practice guideline related to the prescription and management of INR, to take into consideration patient who don’t need a strict INR follow-up (e.g., administration of direct acting oral anticoagulant (DAOC)). A pilot-test will be performed to assess the characteristics of the patients hospitalized at the post-operative cardiac surgery unit and the feasibility of the data collection. The following three additional descriptive variables will be measured for each guideline: 1) number of prescriptions requested by interprofessional teams, 2) proportion of abnormal values below or above normal range, and 3) average of all values of laboratory tests.

Four best-practice guidelines are included in the category of the postoperative assessment performed by interprofessional teams. A daily assessment of the patient’s level of pain, surgical wound(s), nutrition, and mobilization will be measured. For each best-practice guideline recommendation, the achievement of the guideline will be confirmed if at least one postoperative assessment per day is performed by the ACNP or other members of the interprofessional teams during the patient’s hospitalization in the postoperative cardiac surgery unit. The postoperative assessments include the assessment of the clinical manifestations, signs, and symptoms experienced by the patient (e.g., patient’s decrease mobility), as well as the interventions conducted by clinicians following these assessments. Interventions include pharmacological interventions (e.g., prescription of analgesic), non-pharmacological interventions (e.g., prescription of a coronary diet), and clinician consultations (e.g., consultation with the nutritionist). Two additional descriptive variables will be measured for each best-practice guideline, including: 1) the total number of postoperative assessments performed by interprofessional teams during the hospitalization, and 2) the type of associated interventions conducted by clinicians (e.g., non-pharmacological, consultation, etc.).

A composite score will be developed to measure the level of adherence to best-practice guidelines by interprofessional teams with and without ACNPs. A composite score per patient per day of hospitalization in postoperative cardiac surgery will be developed and based on three consecutive steps. Firstly, for each best-practice guideline, a score on a scale of two will be created and points will be attributed for: 1) the achievement of the best-practice guideline recommendation, and 2) the associated intervention performed by clinicians. Points will be given based on the information contained in the patient’s health record and electronic databases. A missed intervention will be considered as a lack of adherence to best-practice guidelines, and no point will be given.

Secondly, an overall composite score will be calculated from the sum of all the scores of all best-practice guidelines (n = 12), ranging from zero to 24. The overall composite score will be transformed into a value in percentage ranging from 0 to 100% (i.e., composite score/24 * 100), such that 100% represents a complete adherence (24/24). An increase of the score will be associated with an increase of the level of adherence to best-practice guidelines by interprofessional teams. An overall score will be calculated per patient per each day hospitalized in the postoperative cardiac surgery unit.

Finally, an average composite score will be calculated from the average of all overall scores during the patient’s hospitalization at the postoperative cardiac surgery unit. An average composite score will be calculated for all patients included in the retrospective cohort.

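### As worded, INR achievement is scored against the normal range, so a day at anticoagulation target can score at most 23/24 while a day with INR still normal can score 24/24

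*Protocol article*

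**What the plan says.** The section on the dependent variable lists potassium, magnesium, serum glucose and INR as the four laboratory guidelines. One achievement rule covers all of them: "The achievement of each best-practice guideline recommendation will be confirmed if the laboratory result falls under the normal range supported by the current literature". The same standard appears twice more in that paragraph. The credited actions are "interventions conducted by clinicians to ensure the laboratory test values remain within the normal range", and a descriptive variable for each test records the "proportion of abnormal values below or above normal range".

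INR has one special provision, a 'no INR needed' variable for patients who do not "need a strict INR follow-up (e.g., administration of direct acting oral anticoagulant (DAOC"). No target or therapeutic INR is given for patients who do need that follow-up.

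Each of the 12 guidelines earns up to two points per day, one for achievement and one for the associated intervention. The sum is divided by 24 and expressed as a percentage, "such that 100% represents a complete adherence (24/24"). The direction is stated: "An increase of the score will be associated with an increase of the level of adherence to best-practice guidelines by interprofessional teams". For each patient, "an average composite score will be calculated from the average of all overall scores" over the stay on the unit. That average is the dependent variable of the linear regression for Objective 3.

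**The concern.** Potassium, magnesium and glucose are managed towards normal values. INR in a patient on an INR-managed anticoagulant is managed towards a treatment target. That this target lies above the normal range is clinical knowledge and an assumption here, because the article prints no INR limits.

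Under that assumption, a team that brings the patient to target loses the INR achievement point, and a team whose patient's INR is still normal keeps it. Prescribing and monitoring anticoagulants is itself one of the four scored pharmacotherapy guidelines, so the score rewards starting the treatment and then penalises its intended effect. The 'no INR needed' variable does not help, because it sets aside exactly the patients to whom the problem does not apply.

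What is at stake is the validity of the dependent variable: for one item, in one group of patients, the score runs against the direction the article states. The extraction tool is also a deliverable in its own right, offered for wider use in cardiac surgery research, so a reversed item would carry over to later users.

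**Working it through.** **Inputs from the article (dependent-variable section):** 12 guidelines; 2 points each per day (achievement, intervention); fixed denominator of 24; INR achievement requires a result in the normal range; ordering and assessing the test count towards the intervention point.

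**Assumed inputs:** the INR target lies above normal; 9 days on the unit (Study setting gives 9 to 11 hospital days on average, about 1 of them in the ICU); the number of days at target and any difference between teams, neither of which the article gives.

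**Step 1. The article's own maximum.** 12 × 2 = 24 points, and 24/24 × 100 = 100%. This agrees with the text. One point is worth 100/24 = 4.17 percentage points.

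**Step 2. Two days in a patient on an INR-managed anticoagulant, the other 11 items full (11 × 2 = 22).** The INR intervention point is available on both days.

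| Day | Rule as worded | Rule against target |
|---|---|---|
| INR at target | 22 + 0 + 1 = 23 (95.83%) | 22 + 1 + 1 = 24 (100%) |
| INR still normal | 22 + 1 + 1 = 24 (100%) | 22 + 0 + 1 = 23 (95.83%) |
| At target minus normal | −4.17 | +4.17 |

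The two rules order the days in opposite ways.

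**Step 3. Patient average.** With k of 9 unit days at target, the highest possible average under the rule as worded is 100 − 4.17 × k/9:

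- k = 3: 98.6%
- k = 6: 97.2%
- k = 9: 95.8%

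**Step 4. Team contrast.** Let d be the difference between teams in the mean share of unit days at target.

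- *Equal normal-INR shares.* The rule as worded gives both teams the same INR achievement credit. The target rule would separate them by d × 4.17. The contrast therefore shifts between rules by 0 (d = 0), 0.42 (d = 0.10) or 0.83 (d = 0.20) points. This is credit that the team with more days at target does not receive.
- *Days at target replace normal-INR days one for one.* The contrast is −d × 4.17 as worded and +d × 4.17 against target, a shift of 2 × d × 4.17: 0.83 points at d = 0.10 and 1.67 at d = 0.20. Only in this case does the INR item reverse between teams.

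**The case against.** The strongest reply is that the deciding definition is not in view. The section Variables under study places the operationalisation of each variable in the S3 Appendix, and the article gives numeric limits for none of the four tests. A range backed by current literature could mean the recommended range, and the existence of the 'no INR needed' variable suggests the authors regard this item as therapeutic monitoring. On that reading, the fault is loose wording in a sentence that covers four tests at once.

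This stands as a limit on the finding: if S3 holds a therapeutic range, only the wording is wrong. It does not remove the point. The article states a rule, applies it to each of the four tests, and repeats the normal/abnormal standard for interventions and for the descriptive variable. The ordinary reading is the more natural one.

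A second reply is that the tool is not final: ten experts review it in two rounds, and a 30-record pilot follows. Those steps could catch the problem, but none is aimed at it. The expert survey rates relevance, and an item can be relevant and still misscored. Kappa measures agreement, and two reviewers can agree on the same wrong score. The five performance measures used for criterion validation include neither INR nor anticoagulants. Only a free-text comment or a team discussion would bring it up.

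A third reply is that no bias between teams is shown. Pairs are matched on type of surgery, and teams are assigned by workload and bed availability, so shares of days at target may well be similar. This is accepted. The differences of 10 and 20 percentage points are illustrations, and the finding concerns the validity of the score, not a demonstrated bias.

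**Conclusion.** The concern holds as worded. A reviewer who follows the text would give a day at INR target at most 23/24 and could give a day with INR still normal 24/24, contrary to the stated meaning of the score. The size is at most 4.17 percentage points on each affected day, diluted when averaged over the stay. The effect on the team contrast is zero if the teams have the same shares of days at target and of normal-INR days, and is otherwise of the order worked out above.

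Two things qualify the conclusion. It assumes that the treatment target lies above the normal range; if it did not, the effect would be zero. And S3 was not seen, so the error may lie in the article's wording alone. With a modest effect and a cheap remedy, this should be corrected, but it does not threaten the study as a whole. Confidence is medium because of S3.

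**What to change.** For patients on an INR-managed anticoagulant, score INR achievement against the target documented in the record, or against the cited guideline's target where none is documented. Apply the same limits to the descriptive variable on abnormal INR values, and word the credited INR interventions to match. Keep the normal range for potassium, magnesium and glucose. The choice of target stays with the treating clinicians and the cited guideline.

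These patients can be identified without a new variable, since for each pharmacotherapy guideline "two additional descriptive variables will be collected, including the type of medication prescribed".

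If S3 already uses a therapeutic range, correct only the sentence in the article. Otherwise, change the rule in both places before the tool goes to the expert committee and the pilot.

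The cost is one scoring rule or one wording change, plus one extra item for reviewers to extract (the INR target), with the guideline fallback for some charts. Under the new rule, a day on which INR is still normal has a maximum of 23/24, including days early in treatment. The authors should confirm that they intend this.

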### Data analysis

Statistical analysis will be conducted to meet objectives one, two and three. The unit of observation will be the patient-level and the unit of analysis will be the interprofessional team with or without ACNP-level.

#### Objective 1

For the content validation [56, 57], a Fleiss Kappa will be calculated for each round of revision and a value between 0.60 and 0.80 will be targeted [48, 49]. The content validity index (CVI) of each individual item of the extraction tool will be calculated from the proportion of experts who rated a score of 4 or 5 on the Likert scale [58]. A CVI of 0.80 will be targeted for each item and items with a value below 0.80 will be removed or modified. Then, the proportion of items with a CVI value above 0.80 will be calculated to determine the overall CVI of the extraction tool. A value higher than 0.80 for the overall CVI of the extraction tool will be targeted [46]. Qualitative comments and recommendations by experts will be analyzed by content analysis [59].

For the criterion validation, Spearman correlation will be calculated to assess the correlation between the measures of the gold standard (e.g., the performance measures of the STS), and the measures of the extraction tool. Values of Spearman correlation higher than 0.70 will be targeted [48, 49].

#### Objective 2

Descriptive analysis will be performed to assess the level of adherence by interprofessional teams with and without ACNPs, as well as the confounding variables for patients under the care of both teams [60]. A graphic illustration will be created to visualize the tendency and distribution of the level of adherence to best-practice guidelines by interprofessional teams with and without ACNPs. An analysis of missing data will be conducted to examine the quality and distribution of missing data within patient health records and electronic databases. Team meetings and consultations with clinicians and statisticians will be held to discuss and identify potential causes of missing data, as well as to conduct a statistical analysis to manage them [61]. Bivariate analysis will be conducted, and the statistical significance will be based on a *p*-value of 0.05 [60]. The Bonferroni correction will be applied for the examination of each confounding variable related to the patient and interprofessional teams’ characteristics [62].

#### Objective 3

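### The daily adherence score is always divided by 24, so a correctly managed patient with a contraindicated drug cannot reach 100%, and the scoring steps do not say how non-applicable items enter

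*Protocol article*

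**What the plan says.** All of the scoring rules stand in the protocol article's section on the dependent variable.

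- For each guideline, "a score on a scale of two will be created and points will be attributed for" two things: achieving the recommendation, and the associated intervention by clinicians.
- The daily total is "calculated from the sum of all the scores of all best-practice guidelines (n = 12), ranging from zero to 24".
- The total becomes a percentage: "The overall composite score will be transformed into a value in percentage ranging from 0 to 100% (i.e., composite score/24 * 100". A total of 24 out of 24 is defined as complete adherence. Daily percentages are then averaged over the patient's stay on the unit.
- On omissions: "A missed intervention will be considered as a lack of adherence to best-practice guidelines, and no point will be given".
- For each of the four drug guidelines, the extra descriptive variables include "the presence of a contraindication, which precludes the possibility of achieving the guideline recommendation (e.g., allergy".
- For the INR guideline, a further variable marking patients who need no strict INR follow-up "will be added specifically for the best-practice guideline related to the prescription and management of INR". Its stated purpose is to take such patients into account.

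Under Variables under study, the operationalization of each variable is placed in S3 Appendix, which is not shown. Under Data analysis, Objective 3, the patient's average composite percentage is the dependent variable of the main regression. Under Objective 1, content validation can change the item list: "items with a value below 0.80 will be removed or modified".

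**The concern.** The plan recognises that some guidelines do not apply to some patients, then writes a formula with no place for that. For contraindicated drugs the conflict is internal. The text says the recommendation cannot be achieved, but the denominator still counts the item. Appropriate care is then scored as incomplete adherence.

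The score therefore mixes two things: how well the team followed the guidelines that applied, and how many applied. The second depends on the patient. It adds variation to the outcome that has nothing to do with team performance. If applicability differed systematically between the teams, that difference would enter the team coefficient, which tests the study hypothesis. As described in the text, neither contraindications nor INR need is among the patient or team covariates or the three matching criteria (age, sex, type of surgery).

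**Working it through.** **Inputs from the protocol.** 12 guidelines; 2 points each; fixed denominator 24; four drug items that can be contraindicated; one INR item that may not be needed. The share of patient-days with a non-applicable item, by team, is not given, so it is an assumption below.

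**Step 1: the plan's own figure.** 12 × 2 = 24, and 24/24 × 100 = 100%. The stated maximum reproduces.

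**Step 2: loss per non-applicable item.** If the intervention point can still be earned, only the achievement point is lost: 1/24 = 4.2 percentage points. If neither can be earned: 2/24 = 8.3 percentage points. The text does not say which applies.

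**Step 3: highest reachable daily score with k non-applicable items.** It is (24 − k)/24 if one point per item is lost and (24 − 2k)/24 if both are.

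| k | One point lost | Both points lost |
|---|---|---|
| 0 | 100% | 100% |
| 1 | 95.8% | 91.7% |
| 2 | 91.7% | 83.3% |
| 5 (all four drugs and INR) | 79.2% | 58.3% |

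With applicable points as the denominator, (24 − 2k)/(24 − 2k) = 100% for every k.

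**Step 4: same care, different score.** Take a team that earns 80% of applicable points, with both points of each non-applicable item lost. The score is 0.8 × (24 − 2k)/24: 80.0% for k = 0, 73.3% for k = 1, 66.7% for k = 2.

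**Step 5: effect on the team contrast.** Per item, the shift is the systematic difference in the share of patient-days where it does not apply, times the loss from step 2.

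| Assumed difference between teams | One point lost | Both points lost |
|---|---|---|
| 5 percentage points | 0.21 | 0.42 |
| 10 percentage points | 0.42 | 0.83 |
| 20 percentage points | 0.83 | 1.67 |

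**Step 6: noise.** Suppose a share p of patients carries a loss L throughout the stay, unrelated to anything in the model. The added SD is L × √(p(1 − p)), and 300 patients carry the information of 300 × s²/(s² + added variance). With an assumed remaining SD of s = 10:

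- one point, p = 10%: L = 4.17, added SD 1.25, about 295 patients;
- one item, both points, p = 10%: L = 8.33, added SD 2.5, about 282;
- one item, both points, p = 40%: added SD 4.1, about 257;
- two items, both points, p = 40%: L = 16.67, added SD 8.2, about 180 (about 231 if s = 15).

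The documents support none of these shares over another.

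**The case against.** Several stronger readings are tempting and are not supported.

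- *The score ignores INR need.* Not shown. The INR variable exists expressly to take these patients into account, it is listed apart from the laboratory descriptive variables, and S3 Appendix may link it to the score. What stands is that the scoring steps in the article do not use it. The contraindication variable differs: the article itself labels it descriptive.
- *Every non-applicable item loses both points.* The no-point rule concerns a missed intervention. Correctly withholding a contraindicated drug need not count as one, so the intervention point may still be earned. Hence the range of 1 to 2 points.
- *Anticoagulant and INR fail together.* The plan's example of a patient without INR need is one on a direct oral anticoagulant. That patient can meet the anticoagulant item, leaving only INR in question.
- *A large part of the sample's information is lost.* This needs the last scenario in step 6. Milder assumptions leave about 257 to 295 of 300, and adjustment for surgery type, comorbidity and surgeon may absorb some of the added variance.
- *The team contrast is biased.* Under Study setting, assignment follows workload and bed availability, not indication, and pairs are matched on surgery type. Chance imbalance is already reflected in the standard error. Only a systematic difference is bias, and none is shown.
- *Dropping an item breaks the score.* With 11 items the literal formula would stop at 22/24 = 91.7%, but the 24 is tied to the 12 items and rescaling is the obvious consequence. This needs only a wording change.

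These objections narrow the point. They do not remove the conflict between the fixed denominator and the statement that a contraindication precludes achievement.

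**Conclusion.** The concern holds in limited form. The article states its scoring formula in full, and for contraindicated drugs that formula conflicts with its own text. For INR the link between the variable and the score is unstated in the article, which is a weaker criticism.

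The firm part is arithmetic: 4.2 to 8.3 percentage points per non-applicable item per day, and a ceiling below 100% for correct care. For INR this assumes that S3 Appendix does not already credit or drop the item. The effect on the comparison is conditional: about 0.4 to 0.8 points per item for each 10-percentage-point systematic difference in applicability. Its actual size and direction cannot be derived, because frequencies by team are not given.

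A reader might infer that the main result will be biased against one team; the documents do not support that. Correction is still warranted because the defect sits in the definition of the dependent variable and is cheap to remove before scoring.

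**What to change.** Define the daily score as points earned divided by points applicable that day, times 100. When a contraindication or the no-INR-needed flag is recorded, remove that item's two points from both numerator and denominator. Base the maximum on the number of items in the final validated tool. Keep the fixed-24 score as a sensitivity analysis. If S3 Appendix already contains such a rule, bring the formula in the article into line with it.

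The cost is one scoring rule, since both flags are already to be collected. There is a real downside. Documentation of contraindications and choice of anticoagulant may differ by team, so the denominator could depend on the exposure. For example, a day with 20 points earned scores 20/24 = 83.3%; if one item that earned nothing is marked as excluded, it scores 20/22 = 90.9%, a gain of 7.6 points. Report the share of excluded items by team, and read the two versions of the score side by side.

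Unavailable source records belong in the missing-data analysis planned under Objective 2. They should not be treated as non-applicable items.
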